## Abstract

**Background:**

There is little evidence on differences across health care systems in choice and outcome of the treatment of chronic low back pain (CLBP) with spinal surgery and conservative treatment as the main options. At least six randomised controlled trials comparing these two options have been performed; they show conflicting results without clear-cut evidence for superior effectiveness of any of the evaluated interventions and could not address whether treatment effect varied across patient subgroups. Cost-utility analyses display inconsistent results when comparing surgical and conservative treatment of CLBP. Due to its higher feasibility, we chose to conduct a prospective observational cohort study.

**Methods:**

This study aims to examine if

1. Differences across health care systems result in different treatment outcomes of surgical and conservative treatment of CLBP

2. Patient characteristics (work-related, psychological factors, etc.) and co-interventions (physiotherapy, cognitive behavioural therapy, return-to-work programs, etc.) modify the outcome of treatment for CLBP

3. Cost-utility in terms of quality-adjusted life years differs between surgical and conservative treatment of CLBP.

This study will recruit 1000 patients from orthopaedic spine units, rehabilitation centres, and pain clinics in Switzerland and New Zealand. Effectiveness will be measured by the Oswestry Disability Index (ODI) at baseline and after six months. The change in ODI will be the primary endpoint of this study.

Multiple linear regression models will be used, with the change in ODI from baseline to six months as the dependent variable and the type of health care system, type of treatment, patient characteristics, and co-interventions as independent variables. Interactions will be incorporated between type of treatment and different co-interventions and patient characteristics. Cost-utility will be measured with an index based on EQol-5D in combination with cost data.

**Conclusion:**

This study will provide evidence if differences across health care systems in the outcome of treatment of CLBP exist. It will classify patients with CLBP into different clinical subgroups and help to identify specific target groups who might benefit from specific surgical or conservative interventions. Furthermore, cost-utility differences will be identified for different groups of patients with CLBP. Main results of this study should be replicated in future studies on CLBP.

## Background

Acute low back pain (ALBP) affects more than 70% of all people at least once in their lifetime [1], and about 5% develop nonspecific CLBP, which is defined as LBP lasting longer than 12 weeks [2]. Although this is only a small group of patients, the economic costs exceed those for the treatment of ALBP by a significant amount [3].

Guidelines already exist for the management of CLBP [4], but the main question in CLBP–whether to offer spinal surgery or conservative treatment–is not clearly answered [5].

With both intervention rates in spinal surgery and health care consumers' expectations rising, critics are voicing concern about a possible "overuse" of spinal surgery [6]. Conservative treatment of low back pain is an alternative that might bridge the self-healing processes [7]. Some authors see advantages for surgical procedures in terms of cost-utility [8], whereas others see no significant differences between both treatment groups [9]. There is weak evidence on differences across health care systems concerning outcomes of CLBP that favours countries with a National Health System (NHS) compared to countries with a private health care system [10,11]. Evidence and outcome-based research is needed to provide information on the appropriate indication for spinal surgery [12]. The aim would be to identify specific target groups that will benefit from specific interventions and classify patients with CLBP into different clinical subgroups [13].

At least six randomised trials have been performed comparing the outcomes of spinal surgery and nonsurgical treatment in CLBP–most of them with some problems in conduct.

Among these are the study by the Swedish lumbar spine study group comparing patients with spinal surgery and patients with continuing physical therapy [14]; the Norwegian spine study comparing patients with lumbar fusion plus physiotherapy, and patients with cognitive intervention plus exercises [15]; the UK Medical Research Council trial comparing patients with spinal stabilisation and patients with an intensive rehabilitation programme [16]; and the American Spine Patient Outcomes Research Trial (SPORT) comparing patients with discectomy and patients with physical therapy plus exercise therapy [17]. Further RCTs have been conducted for spondylolisthesis. Some RCTs had to be closed because patients did not want surgery.

These trials showed conflicting results, with no treatment being clearly superior [18]. Exclusion criteria in all these trials were restrictive; for example, patients with mild CLBP and no need for surgery, as well as patients with progressive neurological abnormalities and surgery were excluded. Recruitment in all trials was long and varied between four and six years. This leads to a reduced generalizability of the results.

The analysis of data from an observational cohort with adequate statistical methods can lead to results with an evidence level 2++. It is slowly recognized that for certain clinical questions RCTs have limitations [19] and may be unnecessary, inappropriate, or impossible to conduct [20].

Feasibility is an important aspect and has been highlighted by the SPORT trial, which consists of a randomised and an observational cohort. The rate of surgical patients with treatment crossover within two years of treatment allocation was 40% in the RCT, compared to merely 4% in the observational cohort [17,21]. The comparable rates of conservative patients' crossover to surgery were 45% and 22%. Currently, a prospective cohort study comparing patients with lumbar fusion and patients with multidisciplinary therapy is under way, for which a randomised cohort design was planned, but was changed to an observational design to minimise a treatment crossover [22].

Therefore, we chose to conduct a prospective observational cohort study as well, with a lower level of evidence than an RCT though, but a higher feasibility.

## Methods/design

### Research plan

#### Objectives and goals

This study aims to identify differences across health care systems in the Swiss and New Zealand populations such as different compensation schemes, patient characteristics, and co-interventions that modify the effects of surgical and conservative treatment of patients with CLBP. In addition, differences in cost-utility will be identified for different groups of patients.

#### Hypotheses

Three hypotheses will be examined:

1. Differences across health care systems result in better treatment outcomes of surgical and conservative treatment of CLBP in countries with a NHS.

2. Patient characteristics, such as high job satisfaction and short pain duration, and co-interventions, such as cognitive behavioural therapy and return-to-work programs, increase the effectiveness of surgical and conservative treatment for CLBP.

3. Cost-utility in terms of quality-adjusted life years (QALYs) is higher in conservative than in surgical treatment of CLBP.

Previous inconclusive findings may have resulted from potential effect modifiers that varied across different health care systems. For instance, expectations to return quickly to work may function as an effect modifier depending on the health compensation system. This study will examine whether the results pertaining to hypotheses 2 and 3 vary by health care system.

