#### Study design

In this multinational prospective cohort study, patients will be recruited consecutively from orthopaedic spine units, rehabilitation centres, and pain clinics in Switzerland (CH) and New Zealand (NZ). Participants will be assessed pre-intervention and at six-month follow-up. The duration of treatment will be a maximum of six months per patient.

The study protocol has been approved by the Ethics Commission of the Canton of Berne (KEK-Gesuchs-Nr.: 191/07).

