#### Cost-utility

The socioeconomic objective of the study is to evaluate the cost-utility outcomes of surgical and conservative treatment of CLBP [8,9,27]. The costs considered include the direct health care expenditures borne by the health care system (insurance, public health care) and out-of-pocket expenditures by patients (medication, alternative medicine, personal prevention activities). The indirect social costs due to lost productivity because of absenteeism also will be accounted for [58]. Direct medical costs will collected from health insurance companies in CH, the NHS in NZ and the clinics in which the patients are selected. Indirect costs and out-of-pocket costs will be measured with a cost diary developed by the Zurich University of Applied Sciences in cooperation with the MEM Research Center. The cost diary will be kept by the patients on a weekly basis covering the total period of treatment with a maximum of six months. At beginning of treatment and end of follow-up period utility will be measured with an index based on EQol-5D and SF-36. Changes in the index will be translated into changes in QALYs.

The cost study of CLBP patients will concentrate on the segment of high-cost patients and address this question: Is this group homogeneous with respect to their socioeconomic status, care-seeking and back pain patterns? If the answer is no, are there subgroups whose cost may be reduced substantially by appropriate (nonmedical) support?

The cost-utility part of the study will be done in collaboration with the Zurich University of Applied Sciences, Institute of Health Economics.

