### Statistical Analysis

#### Outcomes

In this prospective cohort study, two interventions for CLBP are compared: surgical and conservative treatment. Subgroups of different surgical treatments can be distinguished. Nonsurgical co-interventions may have an effect on patient groups with surgical as well as with conservative treatment.

Follow-up data at six months will be analysed according to the intention-to-treat principle, except for those patients who change treatment groups before the beginning of the allocated treatment.

Changes in dependent outcome variables between baseline and follow-up at six months will be analysed by multiple linear regression models. Surgical and conservative treatment, patient characteristics, and co-interventions are independent variables. To address potential effect modification, we will then incorporate interactions between type of treatment and the different co-interventions and patient characteristics.

Highest priority among co-interventions will be given to the analysis of effects of cognitive behavioural therapy and return-to-work programs. Among patient characteristics highest priority in data analysis will be given to gender, age, and duration of work-absenteeism.

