### Feasibility of the study

The patient sample will be taken from orthopaedic spine units, rehabilitation centres, and pain clinics in CH and NZ. The feasibility of data collection in CH has been proved in prior joint ventures between the MEM Research Center and university and regional hospitals (e.g. Inselspital and Salem-Spital in Berne, Schulthess Clinic in Zurich, all of them offering surgical and conservative treatment, none of them working on a referral basis).

NZ has been chosen for comparison of differences across health care systems because of ideal starting conditions for this research project: NZ is a country with a traditionally high acceptance of clinical research. For example, the National Joint Register of patients who underwent total hip or knee replacement, established in 1999, has near 100% coverage.

The MEM Research Center in Berne coordinates the Swiss-based European Spine Registry of the Spine Society of Europe (SSE) [65-70]. In parallel to the planned bi-national multicentre study, a national spine registry for NZ could be implemented by the University of Otago. This National Spine Register – comparable to the existing National Joint Register – would address all patients with CLBP who report to a clinic in NZ, generating synergetic effects. All patients joining the National Spine Register could be asked to participate in the multicentre study as well, which would make data collection much easier.

Cooperation on successful doctoral studies in both countries already exists between the University of Berne and the University of Otago, NZ.

Furthermore, NZ has a manageable population size, which is comparable to CH. This setting and the observational nature of the study will ensure sufficiently high recruitment rates.

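### Hypothesis 1 credits NHS countries, but with one country per system only a Swiss versus New Zealand difference can be estimated, and the stated regression does not test even that validly if centres differ

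*Protocol article*

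**What the plan says.** The first hypothesis (Hypotheses) is directional and causal: "Differences across health care systems result in better treatment outcomes of surgical and conservative treatment of CLBP in countries with a NHS". The same section promises to examine whether the results for Hypotheses 2 and 3 differ by health care system.

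Study design names the sites: "orthopaedic spine units, rehabilitation centres, and pain clinics in Switzerland (CH) and New Zealand (NZ"). Cost-utility shows which system each country stands for: "Direct medical costs will collected from health insurance companies in CH, the NHS in NZ and the clinics in which the patients are selected". Feasibility of the study gives the reason for the second country: "NZ has been chosen for comparison of differences across health care systems because of ideal starting conditions for this research project". Inclusion and exclusion criteria require German in the Swiss sample and English in the New Zealand sample.

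For the analysis, the Outcomes part of Statistical Analysis says "Changes in dependent outcome variables between baseline and follow-up at six months will be analysed by multiple linear regression models" and "Surgical and conservative treatment, patient characteristics, and co-interventions are independent variables". The abstract's Methods describes the same model and does include type of health care system as an independent variable. Demographic and baseline characteristics lists the treating centre among the physician-recorded patient characteristics. Neither the analysis text nor the sample size text mentions a centre term or an allowance for clustering.

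The abstract concludes: "This study will provide evidence if differences across health care systems in the outcome of treatment of CLBP exist". Scientific significance makes a similar claim and expects a possible effect on guidelines.

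**The concern.** There are two separate problems.

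The first is identification. The hypothesis concerns a class of countries, but the design has one member of that class and one comparator. Anything else that differs between Switzerland and New Zealand, such as questionnaire language, surgical practice or referral habits, is carried by the same coefficient. A clear difference between the cohorts could then be reported as an effect of the health care system, in a paper that expects to influence guidelines.

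The second is precision. Patients sit within centres and centres within countries. The country coefficient is therefore a between-centre contrast, yet the model as named is an ordinary patient-level regression. If centres differ at all, that model counts the contrast as better supported than it is, and a chance difference between two sets of centres can look like a country difference.

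**Working it through.** **1. Can the system effect be identified?**

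The documents give two countries and two systems, one country each. Fitting a system effect uses both country-level observations, which leaves 2 − 2 = 0 residual degrees of freedom at country level. Between-country variation unrelated to the system cannot be estimated, and no patient covariate supplies it. Individual compensation status is collected and may vary within a country, but it does not identify an NHS effect.

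The scale of the problem can be illustrated. Take 792 analysed patients (the plan's chain reproduces: 2200 × 0.75 = 1650; × 0.60 = 990; × 0.80 = 792) and the plan's SD of ODI change, 18 to 23. Assume a 1:1 country split, which is not in the document. The naive standard error of the country difference is SD × √(4/792), that is 1.28 points at SD 18 and 1.63 at SD 23.

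Now let countries differ, for reasons unrelated to the system, with SD τ. The variance of the difference becomes SE² + 2τ². A nominal 5% test read as a test of system then rejects with probability 2 × [1 − Φ(1.96 × SE/√(SE² + 2τ²))]:

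| τ (ODI points, assumed) | SD 18 | SD 23 |
|---|---|---|
| 0.5 | 8.6% | 7.2% |
| 1 | 18.9% | 13.8% |
| 2 | 41.9% | 32.7% |

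The study cannot estimate τ, so no analysis of its data can correct for it.

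**2. Is the country contrast itself validly tested?**

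The plan gives no figure for this comparison; its sample size is for treatment-by-modifier interactions. Number of centres, patients per centre (m) and ICC are not stated, so they are assumed, with equal centre sizes.

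- Design effect for a covariate that varies only between centres: DE = 1 + (m − 1) × ICC.
- The correct standard error is √DE times the naive one, so the naive one is too small by 1 − 1/√DE.
- True type I error of a nominal 5% test: 2 × [1 − Φ(1.96/√DE)].

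| m | ICC | DE | Correct SE larger by | Naive SE too small by | True type I error |
|---|---|---|---|---|---|
| 20 | 0.01 | 1.19 | 9% | 8% | 7.2% |
| 40 | 0.02 | 1.78 | 33% | 25% | 14.2% |
| 40 | 0.05 | 2.95 | 72% | 42% | 25.4% |
| 80 | 0.05 | 4.95 | 122% | 55% | 37.8% |

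With only 6 centres (792/6 = 132 patients each) and ICC 0.05, DE is 7.55 and the type I error 47.6%.

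**3. Does entering centre as a covariate solve it?**

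No. The Outcomes text enters patient characteristics as independent variables, and centre is listed among those characteristics. Each centre lies in one country, so the centre indicators sum to the country indicator, and the country coefficient cannot be estimated alongside them. Within ordinary regression, leaving centre out understates the error and putting it in as a fixed effect removes the estimate.

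**The case against.** The strongest reply is that handling of clustering is usually left to a statistical analysis plan, that none is shown, and that this is a condensed article. The text names a model family and nowhere says that patients are treated as independent. Centre is recorded, so a random effect could be added. This stands: it is not established that the final p-value will be too small, only that it would be under the model as stated. Every figure in the clustering table rests on assumed inputs, and the relevant ICC is the residual one after covariate adjustment, which may be lower.

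It can also be said that the wording is partly modest already. The abstract's conclusion is non-directional and asks for replication, the objectives refer to the Swiss and New Zealand populations, and the Background concedes a lower level of evidence than a randomised trial. That is fair, but it does not cure the problem: the hypothesis, the abstract's conclusion and Scientific significance still speak of health care systems.

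A reader might infer four further things that the document does not support:

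- **The plan has no term for Hypothesis 1.** The abstract lists one. The Outcomes text omits it, which is an inconsistency to repair.
- **Recruitment routes differ by country.** The New Zealand register is only a possibility: "All patients joining the National Spine Register could be asked to participate in the multicentre study as well". Study design specifies consecutive recruitment from the same three types of centre in both countries.
- **Clustering distorts the treatment and modifier effects in the same way.** This is not shown. The design effect used here applies to covariates that vary only between centres, and the Swiss example hospitals offer both treatments.
- **The plan has already concluded that NHS countries do better.** That is its hypothesis; its stated conclusion gives no direction.

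**Conclusion.** The identification problem holds on the document alone. With one country per system, the study can estimate a difference between its Swiss and New Zealand cohorts and cannot attribute it to the NHS. The analyses of whether Hypotheses 2 and 3 vary by system carry the same limit. An unseen analysis plan cannot change this, because it follows from the design and the hypothesis.

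The clustering problem is conditional. Its direction is certain for any positive residual ICC under the stated regression. Its size runs from minor to severe over the assumed range of ICC and centre size, and it disappears if an analysis plan not shown already models centre suitably.

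**What to change.** 1. Restate Hypothesis 1, the abstract's conclusion and the claim in Scientific significance as a difference between the Swiss and New Zealand cohorts, with health care system as one possible explanation. Treat the by-system analyses of Hypotheses 2 and 3 in the same way.
2. Name country (health care system) among the independent variables in the Outcomes part of Statistical Analysis, as the abstract does.
3. Fit the outcome models with a random centre effect, test country against between-centre variation with small-sample degrees of freedom, and adjust for centre type (spine unit, rehabilitation centre, pain clinic).

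The cost is some rewording and a mixed model on data already due to be collected. The interval for the country difference will be wider, markedly so with few centres (6 centres leave 6 − 2 = 4 degrees of freedom for the country test before any adjustment for centre type), and the claim more modest. Item 3 makes the Swiss versus New Zealand test sound but does not turn it into a test of health care systems, so item 1 is needed in any case.

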#### Study design

In this multinational prospective cohort study, patients will be recruited consecutively from orthopaedic spine units, rehabilitation centres, and pain clinics in Switzerland (CH) and New Zealand (NZ). Participants will be assessed pre-intervention and at six-month follow-up. The duration of treatment will be a maximum of six months per patient.

The study protocol has been approved by the Ethics Commission of the Canton of Berne (KEK-Gesuchs-Nr.: 191/07).

#### Inclusion and exclusion criteria

We defined broad inclusion criteria to ensure that the spectrum of patients represents the spectrum seen in routine settings: CLBP with a duration of the current episode of at least three months, no relevant improvement under prior conservative treatment for one year, patients about to undergo surgical or further conservative treatment, age 18–65 years at beginning of treatment, good understanding of German in the Swiss patient sample or English the New Zealand sample, and written consent (see table 1).

**Table 1 T1:** Inclusion and exclusion criteria

1. CLBP	7. specific CLBP
2. no relevant improvement under prior conservative treatment for one year	8. acute or subacute LBP
3. about to undergo surgical or further conservative treatment	9. comorbidity that determines overall well-being
4. age 18–65 years at the beginning of treatment	10. pregnancy
5. good understanding of German (CH) or English (NZ)	11. expected loss to follow-up
6. written consent	12. unwillingness to complete questionnaires

Exclusion criteria are specific CLBP (as infection, tumour, osteoporosis, ankylosing spondylitis, fracture, deformity, inflammatory process, and cauda equina syndrome), acute or subacute LBP (defined as LBP continuing for less than six respectively twelve weeks at beginning of treatment [1,4], comorbidity that determines overall well-being (e.g. painful/disabling arthritic hip joints), pregnancy, expected loss to follow-up (e.g. due to removal), and unwillingness to complete questionnaires (see table 1).

